##### Effect modification due to baseline characteristics

We will also explore whether the treatment effects for the two primary outcomes vary by two key individual-level baseline characteristics: sex (female/male) and reported education level (secondary or higher vs. less than secondary). For each primary outcome and each potential effect modifier we will first estimate the covariate-adjusted and covariate-unadjusted cluster-average treatment effect for each of the two subgroups using the cluster-level analysis methods described above (*Main analyses*).

Following the approach of (44) for each potential effect modifier we will then estimate covariate-adjusted and covariate-unadjusted cluster-level measures of treatment effect modification. For the covariate-adjusted analysis this will involve computing the difference between the cluster-average treatment effect for the two subgroups as an estimate of how the cluster-average treatment effect differs between those subgroups (i.e., the cluster-level measure of treatment effect modification). Similar to the cluster-level covariate-adjusted analysis approach described in the *Main analyses* section above, this will involve using an ordinary least-squares linear regression model to adjust for covariates (including the strata) other than the treatment group but also excluding the effect modifier. Using the model, we will then extract the covariate-adjusted residuals for each cluster separately for participants in each effect modifier subgroup and summarize them separately via the mean. We will then compute the difference between these cluster-level subgroup-specific means and use them as the outcome variable in a second ordinary least-squares linear regression model with one covariate for treatment group, with the coefficient for treatment group now giving an estimate of the difference between the cluster-average treatment effect estimates for the two subgroups (i.e., the cluster-level measure of treatment effect modification), along with an associated 95% confidence intervals and *p*-value (with the same adjustment for the stratified approach) (44, 49).

We will treat these effect modification results as exploratory and therefore not adjust them for the multiple testing of the primary outcomes.

##### Effect of engagement with the community dialogue approach intervention

As we do not expect all adult community members to engage with the CDA intervention we will also estimate the individual-level causal effect on the two primary outcomes of (1) having attended one or more CDs (yes/no) and (2) the number of CDs attended (i.e., the linear relationship between the number of CDs attended and the expected mean of the primary outcome). As these treatment effects are non-randomly assigned we will use an instrumental variable approach to try and account for likely confounding, which will estimate these two causal effects among the population of individuals who would be predicted to always comply with the intervention if it was available (i.e., attend the CDs if they were available in their communities) (50). These types of treatment effects are therefore often referred to as complier average causal effects or local average treatment effects (50). Specifically, we will use the two-stage residual inclusion instrumental variable approach with cluster treatment allocation as the instrument, as opposed to the more common two-stage least squares approach, which is more suitable for modeling binary treatments and non-continuous outcomes (51).

To estimate the causal effect on both primary outcomes of attending one or more CDs the two-stage residual inclusion process will involve first fitting a generalized linear model with Bernoulli errors and a logit link to an outcome indicator of whether a survey participant reports having attended one or more CDs, with covariates for cluster treatment allocation, subdistrict, sex (female/male), age (years) and age^2^, education level (none, less than primary, primary, less than secondary, secondary or less than higher secondary, higher secondary, graduate/post-graduate), employment status and main role in the last 30 days (no paid/in-kind work, nonprofessional/manual, personal business, professional), ownership of any animals by the household for food/economic purposes (yes/no), number of individuals living in the household, and the cluster-level baseline mean of the relevant primary outcome. We will then use the model to compute every participants’ model-predicted outcome value based on their observed covariate values, and then subtract those predicted outcomes from a numeric indicator of whether the participant attended one or more CDs (coded as 1) or not (coded as 0) to create residuals for each participant.

We will then fit a second-stage generalized linear model with Poisson errors and a log link to the primary outcome of interest. However, instead of the percentage knowledge scores as outcome values we will analyze the raw count of correct/appropriate answers, as appropriate for the Poisson distribution. The model will contain covariates for whether the participant reported attending one or more CDs (yes/no), the residual computed in the first-stage model, and all the other covariates included in the first-stage model.

Using this model, we will then use marginal effects methods to estimate the treatment effect by computing each participants’ model-predicted count of correct/appropriate answers based on their observed covariate values except for attending one/more CDs, which will be first set to yes for all participants (and predictions saved) and then no for all participants (and predictions saved). We will then convert these predicted counts of correct/appropriate answers to predicted percentages of correct/appropriate answers by dividing by the relevant number of questions asked for that knowledge score and multiplying by 100. Lastly, we will take the mean of each set of predictions and take their difference. This will estimate the causal effect of attending one/more CDs as the mean difference in the relevant percentage knowledge score for those attending one/more CDs compared to those attending no CDs, among those who would be predicted to always attend CDs if they were available in their community.

As a sensitivity analysis we will also repeat these analyses but at the second stage use generalized linear models with Gaussian errors and identity links instead, with the relevant percentage knowledge scores as the outcome, to compare with the results based on the Poisson model.

For statistical inference we will estimate 95% confidence intervals for all these treatment effects via a stratified, clustered bootstrap approach (52), to account for the clustered structure of data. This will involve resampling clusters within subdistricts while maintaining a 1:1 treatment allocation of the clusters within each bootstrapped subdistrict dataset, and using a modification of the bias-corrected accelerated method to compute the 95% confidence intervals from the bootstrapped data (53) (based on 5,000 resamples).

For an instrumental variable analysis to produce an unbiased estimate of the treatment effect of interest there are four key assumptions that must be met (54). Although there are many other possible sources of bias, and meeting these assumptions does not guarantee an unbiased estimate, we believe the analysis will not at least not violate these assumptions in any substantial way. (1) The instrument must be conditionally randomized with respect to the outcomes of interest and the treatments of interest. As we will be using the random allocation of clusters to the assigned treatment group as the instrument this assumption will be satisfied. (2) The instrument must effect the treatments of interest. Unless there are no survey participants in the intervention group communities who engage with the intervention this assumption will be satisfied. (3) The instrument must have no direct effect on the outcomes of interest and only affect them indirectly via the treatments of interest (commonly known as the exclusion restriction). As we are using the random allocation of clusters to treatment groups as the instrument this random allocation itself clearly has no causal effect on the outcomes of interest (only the treatment implemented, which may or may not be received by a participant), and so this assumption will be satisfied. (4) There are no survey participants who would attend CDs if they were available in their communities and if they were not encouraged to attend, but who would, conversely, not attend any CDs if they were available in their communities and if they were encouraged to attend (the community volunteers running the CDs will be encouraged to encourage members of their community to attend CDs). This is more speculative but, given the unusual behavior required, if such individuals do exist we believe they will be very infrequent.

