#### Primary outcome 1: percentage of correct/appropriate responses to 25 questions assessing knowledge about antibiotics, antibiotic resistance, and usage of antibiotics for human illness

Our first primary outcome measures individuals’ level of correct and appropriate knowledge about antibiotics (e.g., whether or not antibiotics can kill viruses, whether or not antibiotics can be delivered via pills, injections, creams etc), ABR (e.g., whether or not ABR can occur due to your body becoming “resistant” to antibiotics), and usage of antibiotics for human illness (e.g., whether it is appropriate and safe to share antibiotics with family/friends). We will ask survey participants a series of 25 factual, multiple-choice questions on these topics. Most of the questions will allow respondents to choose from a binary response (e.g., “yes” or “no,” or “appropriate” or “inappropriate”) but a few include more than two options, and all allow the respondent to choose “do not know.” Correct responses will receive a score of 1 and incorrect or “do not know” responses a 0 (see *Survey questionnaire* in Supplementary file 2 for a full list of the questions). We will then convert the overall score to a percentage of correct/appropriate responses for analysis. We are therefore implicitly treating all questions as equally important. This outcome will allow us to assess whether the CDs improve the level of correct and appropriate knowledge about antibiotics, ABR, and usage of antibiotics for human illness.

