#### Primary outcome 2: Percentage of correct/appropriate responses to 20 questions assessing correct/appropriate knowledge about usage of antibiotics for animal health and antibiotic-related environmental considerations

Our second primary outcome will also measure individuals’ knowledge but will focus on correct and appropriate knowledge about usage of antibiotics for animal health (e.g., prophylaxis and growth promotion as well as disease) and antibiotic-related environmental considerations. For this outcome we will ask 20 multiple-choice questions, which will be scored in the same way as the previous knowledge outcome and again converted to a percentage for analysis (see *Survey questionnaire* in Supplementary file 2 for a full list of the questions). This outcome will allow us to assess whether the CDs improve the level of correct and appropriate knowledge about the usage of antibiotics for animal health and antibiotic-related environmental considerations (the other main aspects of a One Health perspective on antibiotics and ABR).

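### The supporting engagement analysis fits a score capped at 25 or 20 as an unbounded Poisson count with a log link, so predictions can pass 100% and the averaged effect can be biased in either direction

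*Protocol article*

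**What the plan says.** The two knowledge scores have fixed maxima. For primary outcome 1, "We will ask survey participants a series of 25 factual, multiple-choice questions on these topics"; for primary outcome 2, "For this outcome we will ask 20 multiple-choice questions". Each item is scored 1 or 0 ("Correct responses will receive a score of 1 and incorrect or" don't-know answers get 0), and the second score is built in the same way.

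The engagement analysis uses two-stage residual inclusion with cluster allocation as the instrument. For its second stage the protocol says: "We will then fit a second-stage generalized linear model with Poisson errors and a log link to the primary outcome of interest". It justifies the response variable thus: "we will analyze the raw count of correct/appropriate answers, as appropriate for the Poisson distribution". The effect of attendance comes from predictions for every participant, with attendance "which will be first set to yes for all participants (and predictions saved) and then no for all participants". Predicted counts become percentages by "dividing by the relevant number of questions asked for that knowledge score and multiplying by 100", and the two sets are averaged and differenced. The text mentions no binomial denominator and no upper limit.

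A Gaussian identity-link model on the percentage score is planned as a sensitivity analysis. Confidence intervals come from a stratified cluster bootstrap.

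**The concern.** A number correct out of a known total is a binomial-type quantity. The Poisson variance is the lesser matter, since the bootstrap does not rely on it. The mean model is the real difficulty. A log link makes the effect of attendance multiplicative, so those who already score highest are assigned the largest percentage-point gain although they have the least room to improve, and nothing holds a prediction at or below 100%.

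The multiplier is learned from attenders but applied to everyone. If attenders differ in level from the rest, the averaged percentage-point difference moves away from the true one. The protocol expects confounding of attendance; that is its reason for using an instrument. The choice also sits oddly with the rest of the plan, which prefers residual inclusion because it suits binary treatments and non-continuous outcomes, and which uses Bernoulli/logit models for its binary secondary outcomes.

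**Working it through.** **1. Scale of the score.** The engagement analysis states no figure of its own, so the plan's sample size result is used to fix the scale. Inputs from *Sample size*: variance 40, ICC 0.3, 44 participants per cluster, 25 clusters per arm, alpha 0.025 (taken as two-sided), power 90%.

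Detectable difference = (2.241 + 1.282) × √[2 × 40 × (0.3 + 0.7/44)/25] = 3.523 × 1.005 = 3.54 answers; 3.54/25 = 14.2 points. The plan states 14. The variance of 40 is therefore on the count scale, and the SD is √40/25 = 25.3 percentage points.

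**2. What the log link implies.** Assumed: a 50% mean without attendance, 50% attendance in the intervention arm, and an effect only through attendance. The plan's 15-point target by allocation then implies 15/0.5 = 30 points among attenders. The multiplier is 80/50 = 1.6.
- A participant predicted at 30% goes to 48% (gain 18).
- A participant predicted at 70% goes to 112% (gain 42).
- Anyone predicted above 100/1.6 = 62.5% without attendance passes 100% with it.

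**3. Share above 100%.** Normal approximation, with the spread of predictions set by the share of variance the covariates explain (assumed):
- 10% explained: SD √0.1 × 25.3 = 8.0; (62.5 − 50)/8.0 = 1.56; about 6% of participants.
- 30% explained: SD √0.3 × 25.3 = 13.9; 12.5/13.9 = 0.90; about 18%.

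**4. Direction of the bias.** Suppose attendance truly adds 20 points for everyone and the overall mean without attendance is 50% (illustrative).
- Attenders start at 40%: multiplier 60/40 = 1.5; average over all, 50 × 0.5 = 25 points (too large).
- Attenders start at 60%: multiplier 80/60 = 1.33; average over all, 50 × 0.33 = 16.7 points (too small).
- Averaged over attenders only, both give 20 (40 × 0.5 and 60 × 0.33).

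**5. Simulation.** 50 clusters of 44, two-stage residual inclusion, allocation left out of stage two so that only the link is tested. Knowledge level, attendance and effect are assumed throughout.

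With a control mean of 35–50%, attendance of 25–50% and a true effect of about 19 points, 4–18% of participants were predicted above 100%. Poisson estimates were about 22–25 when attenders score lower and 9–16 when they score higher (18 in a variant with weaker covariates and no unmeasured confounding). Binomial-logit estimates were 17.5–19.4. The pattern held under a truncated-linear data model, which does not favour the logit.

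A second grid (25 items) shows the role of confounding. Settings shown: control mean 50%, attendance 50%; entries are mean estimate (SD), in points.

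| Attendance | True, compliers / all | Poisson | Binomial | Gaussian | Above 100% |
|---|---|---|---|---|---|
| Confounded | 20.0 / 20.9 | 16.1 (5.1) | 20.9 (4.1) | 19.4 (4.4) | 8.5% |
| Confounded | 28.0 / 29.9 | 22.4 (5.4) | 30.0 (3.7) | 27.0 (4.4) | 12.5% |
| Not confounded | 20.0 / 20.0 | 20.1 (5.7) | 19.7 (3.9) | 19.8 (4.3) | 10.9% |
| Not confounded | 28.0 / 28.0 | 28.2 (6.0) | 27.7 (3.5) | 27.9 (4.3) | 17.2% |

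Over that whole grid and its variants, the share above 100% ran from 0 to 19.5% (0–7.7% with weakly prognostic covariates). The Poisson SD was 1.03 to 2.8 times the binomial SD and about 1.04 to 1.7 times the Gaussian SD.

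**The case against.** The strongest defence is that the consequences depend on facts the protocol does not supply. It gives no expected score, attendance rate or engagement effect. Only about half of adults in this setting report having heard of antibiotics, and don't-know answers score 0, so low means, with few predictions near the ceiling, are plausible. This stands: a reader might infer that many participants will be predicted above 100%, and the document does not support that.

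A reader might also infer that predictions above 100% must inflate the estimate. They need not: in the table the Poisson estimate is too low where attendance is confounded and nearly unbiased where it is not, although 8.5–17.2% of predictions exceed 100% in all four rows. The sign depends on who attends.

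Third, much of the error comes from averaging over all participants. Averaged over attenders only, the Poisson root mean squared error was only about 2–19% larger than the binomial one. That stands as a limit on size, but the plan does average over everyone.

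Fourth, safeguards exist. The bootstrap keeps the wrong Poisson variance from invalidating the intervals by itself, and the Gaussian model came within about 12% of the complier effect in the main grid. Neither repairs the headline estimate: the bootstrap does not correct a wrong mean model, and the Gaussian result is labelled a sensitivity analysis.

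**Conclusion.** The point holds as a mis-specified second stage in a supporting analysis. The protocol states the Poisson/log choice and gives a reason for it, so this is not detail left to the analysis plan, and the reason is wrong for a score with a fixed ceiling. Predictions above 100% are possible (about 0–20% of participants over the assumed settings). The headline percentage-point effect can be too large when attenders score lower than others and too small when they score higher. It is often less precise than under a bounded model, though at the low end of the range the loss is negligible. The bias is small when attendance is unrelated to score.

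All these sizes rest on assumed knowledge levels, attendance, effects and data models. They also leave allocation out of stage two. Read literally, the protocol carries every other first-stage covariate, including allocation, into stage two; simulations that kept it there gave conflicting results and are not relied on. Nothing here touches the primary treatment effects, which come from the cluster-level regression on percentage scores.

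**What to change.** In *Effect of engagement with the community dialogue approach intervention*, replace the Poisson/log second stage by a binomial, or quasi-binomial, model with a logit link for the number correct out of 25 (primary outcome 1) or 20 (primary outcome 2). Delete the statement that the raw count suits the Poisson distribution. Keep the first-stage residual, the non-instrument covariates, the marginal-effects step on the percentage scale, the cluster bootstrap and the Gaussian sensitivity analysis.

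The cost is one line of wording and a change of family and link in the code, with no new data.

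Two separate questions remain after this change: whether allocation, the instrument, belongs in stage two, and whether averaging over all participants matches the stated complier interpretation. On the second, the all-participant effect that averaged binomial predictions target differed from the complier effect by up to about 25% in the simulations.

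### As written, the second stage of the attendance (instrumental-variable) analysis keeps cluster allocation, the instrument, as a covariate, so the randomized contrast no longer identifies the effect; separately, an all-participant average is labelled a complier effect

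*Protocol article*

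**What the plan says.** All of this is in the protocol article, section *Effect of engagement with the community dialogue approach intervention*.

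- Method: a "two-stage residual inclusion instrumental variable approach with cluster treatment allocation as the instrument".
- First stage: a logit model for having attended at least one dialogue, "with covariates for cluster treatment allocation, subdistrict, sex (female/male), age (years" and the remaining individual and cluster covariates. Allocation is the first covariate listed. The residual is observed attendance minus fitted probability.
- Second stage: "a second-stage generalized linear model with Poisson errors and a log link to the primary outcome of interest", using the raw count of correct answers. Its covariates are attendance, "the residual computed in the first-stage model, and all the other covariates included in the first-stage model".
- Effect: predictions with attendance "first set to yes for all participants (and predictions saved) and then no for all participants (and predictions saved", converted to percentages, averaged and differenced. The result is described as the effect among people who would attend if dialogues were available to them.
- Sensitivity analysis: a Gaussian, identity-link second stage on the percentage score. No change of covariates is mentioned.
- Assumptions: the third listed condition is that the instrument acts on the outcome only through the treatment of interest, and the plan says this is met.

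**The concern.** Attendance is the outcome of the first stage, not one of its covariates, so taking all the other first-stage covariates into the second stage removes nothing, and allocation stays in. An outcome model with an allocation coefficient gives allocation a direct effect, which the plan's exclusion restriction rules out. That coefficient also takes up the difference between arms, which is the only randomized information about what attendance does. The reported effect changes attendance alone and holds other covariates at their observed values, so whatever allocation has absorbed is left out.

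At stake is the plan's only estimate of what attending dialogues does to the two primary outcomes. It could be too imprecise to use, or near zero when attendance works, and the planned sensitivity analysis would not reveal this.

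The averaging step raises a separate, smaller question. Under a log link, a difference averaged over everyone, including people who would never attend, is not in general the effect among compliers.

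**Working it through.** The article gives no figure for this analysis, so there is none to reproduce. The check has three parts.

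**1. Identification.** Write Z for allocation, X for the other covariates, D for attendance, p(Z,X) for fitted attendance and R = D - p(Z,X). Then D - R = p(Z,X). Without X, p is a linear function of Z, so the columns 1, D, R and Z are linearly dependent. The matrix has rank 3 of 4, and the coefficient of D is not identified.

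**2. What identifies the effect once X is added.** Take a linear second stage, no attendance in control clusters, and two covariate groups of equal size with intervention-arm attendance p1 and p2 and attendance effects t1 and t2. The arm differences within the groups are p1·t1 and p2·t2. The coefficient of D is then:

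- Z kept: (p2·t2 - p1·t1) / (p2 - p1)
- Z dropped: (p1²·t1 + p2²·t2) / (p1² + p2²)

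If t1 = t2 = t, both equal t, but the first divides by the usually small difference p2 - p1 and is therefore imprecise. If the effects differ, the second is still a positively weighted average of t1 and t2. The first is not: with p1·t1 = p2·t2 it is exactly zero although both effects are positive, and if the group that attends less gains enough more, it is negative. If the group that attends more gains more, the first exceeds both effects.

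**3. Size, by simulation** (300 replicates per scenario).

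- From the article: 50 clusters of 44, 5 strata, a 25-item score, the stated logit first stage and Poisson or Gaussian second stage.
- Assumed, because the article does not give them: about 30% attendance in the intervention arm; 0% or 3% in control; an unmeasured confounder; baseline score about 36%; rate ratio 1.4 or 1.0; between-cluster SD of the log mean 0 or 0.15; strong or weak prediction of attendance by covariates; an effect that is constant, larger in the less educated, or varying with the confounder.

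Mean (SD) in percentage points, for between-cluster SD 0.15 and no control attendance:

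| Effect; covariates | Complier truth | Poisson, Z kept | Poisson, Z dropped | Gaussian, Z kept | Gaussian, Z dropped |
|---|---|---|---|---|---|
| Constant ratio; strong | 16.2 | 17.1 (8.9) | 14.8 (6.0) | 21.9 (7.5) | 16.5 (5.2) |
| Constant ratio; weak | 16.0 | 26.5 (91.3) | 14.5 (6.4) | 23.2 (22.3) | 15.9 (5.3) |
| By education; strong | 14.7 | 1.0 (8.2) | 12.4 (6.0) | 6.0 (7.8) | 14.1 (5.2) |
| By education; weak | 15.2 | 4.7 (42.1) | 12.9 (5.9) | 6.7 (24.9) | 14.3 (5.0) |
| By confounder; strong | 20.0 | 15.9 (9.7) | 17.7 (5.9) | 22.6 (8.2) | 20.0 (4.8) |
| None; strong | 0.0 | 1.2 (7.6) | 0.0 (4.4) | 1.1 (7.8) | 0.0 (4.5) |
| None; weak | 0.0 | 6.7 (27.7) | 0.4 (4.8) | 2.8 (20.9) | 0.3 (4.9) |

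In the weak rows a few extreme replicates pull the Poisson means with Z kept: the medians are 16.3 (constant ratio), -0.8 (by education) and 3.4 (none).

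Across all scenarios run:

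- Poisson, Z kept, constant ratio, strong covariates: mean 14.8 to 17.1 against about 16, so little bias, with SD 6.0-11.2 against 1.7-6.6 with Z dropped.
- Poisson, Z kept, effect larger in the less educated: mean -2.9 to 4.7 against about 15. The largest bias is 15.0 - (-2.9) = 17.9 points.
- Poisson, Z kept, weak covariates: SD 11.0-91.3 against 1.4-6.7 with Z dropped.
- Poisson, Z dropped: the average over everyone falls short of the complier effect by, for example, 16.2 - 14.8 = 1.4 and 14.6 - 11.8 = 2.8 points. This is the averaging mismatch.
- Gaussian, Z dropped: within about 1 point of the complier truth throughout.

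**The case against.** The wording may be a drafting slip. Two-stage residual inclusion with allocation as the instrument, and an explicit exclusion restriction, both imply that allocation was meant to stay out of the second stage, and the article says it only summarizes the analysis ahead of a full plan. This is plausible, but it does not remove the point, because the article fixes the covariate list itself. Where the authors want treatment left out they say so: *Main analyses* excludes the treatment variable from its first-stage model, and *Effect modification due to baseline characteristics* does the same. *Subgroup-specific secondary outcomes* uses almost the same phrase about first-stage covariates for a model in which allocation must remain. A programmer following the text would keep it.

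A reader might go further and infer that the estimates will be badly biased. The documents do not support that. With a constant rate ratio and strong covariates the literal model was nearly unbiased, and the large errors came from effect heterogeneity that was assumed. The real covariate list is also long, so the weak-covariate scenarios may not represent it. On the other side, the plan itself treats modification by sex and education as worth testing, so such heterogeneity is not far-fetched.

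A reader might also infer that two-stage least squares must become the main estimator. The plan gives its reason for preferring residual inclusion ("as opposed to the more common two-stage least squares approach, which is more suitable for modeling binary treatments and non-continuous outcomes"), and its Gaussian version without allocation already performs well. The cap of 25 or 20 items on the count was not shown to matter by itself.

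**Conclusion.** The point holds in two parts of unequal weight.

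First, the second stage as written contains the instrument, contradicts the plan's exclusion restriction and loses identification by the randomized contrast. This follows from the text and the algebra and needs no simulation. Precision was worse in the Poisson scenarios tabulated, from modestly (8.2 against 6.0) to severely (91.3 against 6.4). Bias of about 1 to 18 points, possibly to near zero or the wrong sign, is what can happen; its size depends on attendance, confounding and heterogeneity that the article does not state.

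Second, the average over all participants is a complier effect only under homogeneity. The mismatch was about 1-3 points once allocation was dropped, so this is mainly a matter of naming the estimand correctly.

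The analysis is supplementary. The primary cluster-level comparison by randomized allocation is not affected.

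**What to change.** 1. State that the second stage, in both the Poisson and the Gaussian version, includes attendance, the first-stage residual and all first-stage covariates except cluster treatment allocation. Apply the same clause to the analysis of number of dialogues attended if it uses the same second stage.
2. Either average the predicted differences over the complier population, or keep the average over all participants, relabel the estimand accordingly and state the homogeneity assumption under which it equals the complier effect.
3. Optional: report two-stage least squares on the percentage score with the same covariates. It is not needed for a nearly unbiased linear estimate, since the planned Gaussian version supplies one once allocation is excluded.

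The cost is a few sentences in the analysis plan promised before database lock and a small change to the code. No data collection, sample size or primary analysis changes.
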